# Minimally invasive right colectomy anastomosis study (MIRCAST): protocol for an observational cohort study of surgical complications using four surgical techniques for anastomosis in patients with a right colon tumor

**DOI:** 10.1186/s12893-020-00803-x

**Published:** 2020-07-13

**Keywords:** Anastomosis, Colectomy, Complications, Endoscopy, Extracorporeal, Intracorporeal, Laparoscopy, Robot-assisted surgery

## Abstract

**Background:**

Right colectomy is the standard surgical treatment for tumors in the right colon and surgical complications are reduced with minimally-invasive laparoscopy compared with open surgery, with potential further benefits achieved with robotic assistance. The anastomotic technique used can also have an impact on patient outcomes. However, there are no large, prospective studies that have compared all techniques.

**Methods/design:**

MIRCAST is the Minimally-Invasive Right Colectomy Anastomosis Study that will compare laparoscopy with robot-assisted surgery, using either intracorporeal or extracorporeal anastomosis, in a large prospective, observational, multicenter, parallel, four-cohort study in patients with a benign or malignant, non-metastatic tumor of the right colon. Over 2 years of follow-up, the study will prospectively evaluate peri- and postoperative complications, postoperative recovery, hospital stay, and mid-term results including survival, local recurrence, metastases rate, and conversion rate. The primary composite endpoint will be the efficacy of the surgical method regarding surgical wound infections and postoperative complications (Clavien-Dindo grade III-IV complications at 30 days post-surgery). Secondary endpoints include long-term oncologic results, conversion rate, operative time, length of stay, and quality of life.

**Discussion:**

This will be the first large, international study to prospectively evaluate the use of minimally-invasive laparoscopy or robot-assisted surgery during right hemicolectomy and to control for the impact of the anastomotic technique. The research will contribute to current knowledge regarding the medical care of patients with malignant or benign tumors of the right colon, and enable physicians to determine which technique may be the most appropriate for their patients.

**Trial registration:**

This study was registered on Clinicaltrials.gov (clinicaltrials.gov identifier: NCT03650517) on August 28th 2018 (study protocol version CI18/02 revision A, 21 February 2018).

## Background

The standard surgical treatment for malignant neoplasms of the right colon is right colectomy (hemicolectomy). Open resection is associated with a relatively high rate of complications, but these may be reduced along with blood loss and hospital stay using laparoscopy [1, 2], a minimally-invasive technique in which operations are performed via small incisions (usually 0.5–1.5 cm) at a location distant to the site of interest. There are some limitations to the laparoscopic approach, including loss of a three-dimensional view, poor ergonomics, limited movement dexterity, and tremor [3], which may be overcome with robotic assistance. This minimally-invasive approach offers greater precision, flexibility, and control that minimizes the risk of injury to vessels and nerve structures, and enables oncologic resection [4]. Although longer operative times have been reported with robot right colectomy, the surgery can significantly reduce blood loss, postoperative complications and wound infections, lead to faster recovery of bowel function, fewer conversions to open surgery, and shorter hospital stay compared with laparoscopy [5, 6]. It should be noted that in many studies to date, the operating surgeon was often relatively inexperienced in robot-assisted surgery [5]; operative times can improve significantly with increasing experience [7]. There are also potential advantages in performing intracorporeal anastomosis (ICA, where the anastomosis is performed inside the abdominal cavity during minimally-invasive surgery) compared with extracorporeal anastomosis (ECA, where the anastomosis is performed by pulling out the bowel through a laparotomy). Benefits of ICA include smaller incision length, reduced time to first defecation, reduced short-term morbidity (e.g. less surgical wound infection), decreased rate of incisional hernias and re-interventions, and a shorter hospital stay compared with ECA [8, 9]. It is possible that the ability of the surgeon to perform ICA may be enhanced by robotic assistance, potentially reducing the conversion rate and improving the quality of suturing, but further research is required.

To date, many comparative studies of laparoscopic and robot-assisted right colectomy have been small, retrospective, non-randomized studies that did not control for anastomosis technique or the effect of robotic assistance on anastomosis. Prospective, multicenter studies that simultaneously compare both variables (i.e. surgical approach and anastomotic technique) are needed to provide evidence regarding the best technique for minimally-invasive right colectomy. Therefore, we have developed the Minimally-Invasive Right Colectomy Anastomosis Study (MIRCAST) (Fig. 1), a large prospective, observational, multicenter, parallel, four-cohort study designed to compare ICA and ECA after a minimally-invasive right colectomy, each using either laparoscopic and robotic-assisted approach, in patients with a benign or malignant, non-metastatic tumor of the right colon.

**Fig. 1 Fig1:**
[figure not shown]
Study schematic. ECA, extracorporeal anastomosis; ICA, intracorporeal anastomosis

## Methods/design

### Patient recruitment

Patients included in the study will be adults (male or female aged ≥18 years) with a benign or malignant tumor in the right colon that require an elective right colectomy with curative intent. Patients will have a life expectancy of at least 12 weeks, with an adequate performance status (Eastern Cooperative Oncology Group Scale score ≤ 2). All patients will have voluntarily signed and dated an Ethics Committee-approved informed consent form before inclusion, obtained by the investigator or designee. Patients will be excluded if they have cT4b tumors, metastatic disease, planned colonic surgery along with other major concomitant procedures (e.g. liver resections, other intestinal resections), or have inflammatory bowel disease (i.e. Crohn’s disease or ulcerative colitis). Patients who are pregnant or suspected to be pregnant, have a comorbid illness or condition that would preclude the use of surgery, are undergoing emergency procedures, or are unwilling to comply with all follow-up study requirements will also be excluded. All patients will be screened and recorded during enrolment to identify any selection bias, which can be higher in observational studies [6].

Eligible patients will be recruited from the approved participating centers according to the surgeons’ experience with each technique. It is calculated that at least 1200 patients (300 per cohort) should be enrolled in the study. The assumptions for the sample size were based on the incidence of surgical wound infection and Clavien-Dindo grade > IIIa complications. The sample size is based on attaining a success rate of 85% for the primary endpoint, with the lower 95% confidence limit being no greater than 5% from the estimated success rate. Assuming a 2-sided interval, a total of 245–317 patients will be required within each cohort. Accounting for a 10% loss to follow-up, a total of 1200 patients will be recruited so that the four parallel cohorts will have sufficient power to make multiple comparisons.

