### Statistical analysis

All analyses is detailed in a statistical analysis plan. Patients from each cohort will be analyzed separately on an intent-to-treat basis. Descriptive statistics will be provided for all discrete variables in the form of rates and proportions with 95% confidence intervals (CI). Continuous variables will be escribed by mean, standard deviation, median and range. Overall survival, disease-free survival, local recurrence rate and metastasis rate will be estimated using the method of Kaplan Meier. Exploratory comparisons of discrete variables will be performed using a Chi-squared test, using continuity correction or Fisher’s exact test. Continuous variables will be compared using a Student’s t-test, or a non-parametric equivalent (Wilcoxon). Survival statistics will be based on a stratified log-rank test. All tests will be two sided with a *p*-value of less than 0.05 considered to indicate statistical significance.

An interim analysis is planned after having recruited 300 patients, 75 patients at least per cohort, in order to evaluate whether a success rate around 85% is achieved for each cohort; a lower limit of 75% is not acceptable, for which reason the data from the treatment groups with a success rate < 75% will be excluded from further analysis. None a priori expectations of differences can be made based in current literature.

A propensity score will be constructed as the individual prediction (in logit scale) of a logistic regression model in which the outcome is modeled with different potential confounding factors. The propensity score will be added as a continuous variable to adjust the risk models. The Generalized Linear Model (GLM) approach allows for the construction of multilevel and mixed models, which will be useful for controlling the inter-hospital random variability.

Secondary end-points will be analysed according to their characteristics: GLM with identity link will be used for operative time, number of harvested lymph nodes and length of stay, GLM with logit link will be used for unplanned conversion, complete mesocolic excision and R0 resection and Cox regression will be used for middle-term oncologic results: overall survival, disease-free survival, local recurrence and metastasis.

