### Sample size calculation

The assumptions for the sample size of this study have been developed based on the incidence of Surgical Wound Infection, as well as the incidence of Clavien-Dindo grade > III complications as seen in the Introduction. The sample size is based on attaining a success rate of 85% for the primary endpoint, with the lower 95% confidence limit being no greater than 5% from the estimated success rate. Assuming a 2-sided interval, a total of 245–317 subjects will be required within each cohort. Accounting for a 10% loss to follow up, a total of 1200 subjects will be recruited for this study. Several interim analysis are planned through the study in order to build new power analysis and adjust sample size accordingly if needed.

The design of this study envisages four parallel cohorts for which the sample size has been developed for each cohort according to a precision around an expected success rate with enough subject and sufficient power to make multiple comparisons within the appropriate method. Any statistical inferences drawn based on pairwise comparisons will be undertaken in a posteriori statistical analysis using a propensity score to account for confounding covariates.

The primary endpoint for success is defined as a patient meeting the following criteria:
Surgical Wound Infection 5% lower in the ICA group.Grade IIIb-IV Clavien -Dindo complications at 30 days post op 5% lower in the ICA group.

According to the current literature the the following numbers represent Surgical Wound Infection and Severe Complications in intermediate volume centers:

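### The sample-size text does not reconcile 245–317 per cohort with 1,200 recruited, claims power that was never calculated, and words a between-group difference as a patient's success

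*Protocol article*

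**What the plan says.** Under Patient recruitment, the sizing rule is single-cohort precision: "The sample size is based on attaining a success rate of 85% for the primary endpoint". The allowed margin is then set out in these terms: "with the lower 95% confidence limit being no greater than 5% from the estimated success rate". The result is "Assuming a 2-sided interval, a total of 245–317 patients will be required within each cohort". With 10% loss to follow-up the total is set at 1,200, or 300 per cohort, and the text adds that "a total of 1200 patients will be recruited so that the four parallel cohorts will have sufficient power to make multiple comparisons". Sample size calculation repeats the requirement ("a total of 245–317 subjects will be required within each cohort") and the power claim. It also plans interim analyses to redo the power analysis and adjust the size, and places pairwise inference in a later propensity-score analysis.

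The same section defines patient success by two bullets. One is "Surgical Wound Infection 5% lower in the ICA group"; the other is the same 5% reduction for Clavien-Dindo IIIb-IV complications. A table of literature rates follows: wound infection 4–5% (ICA) and 10–14% (ECA); grade 3b-4 morbidity 1.1–5% (ICA) and 8–11% (ECA).

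Outcomes defines the primary endpoint differently. A patient scores 1 if either a wound infection or a grade IIIb-IV complication occurs.

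Statistical analysis says "Patients from each cohort will be analyzed separately on an intent-to-treat basis", sets significance at p "less than 0.05 considered to indicate statistical significance", calls the simple tests of discrete variables exploratory, and states that the literature supports no prior expectation of differences.

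**The concern.** Three parts of the text do not fit together.

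- **Size.** The requirement, the loss allowance and the total do not reconcile at the upper end of the range.
- **Power.** A precision calculation for one cohort says nothing about power to compare cohorts. The text nevertheless asserts that power, without a contrast, a composite effect, an alpha for multiple comparisons or a power figure.
- **Endpoint.** A difference between groups is written as something a patient achieves. This conflicts with the patient-level composite in Outcomes. It also sits badly beside the statement that no differences can be expected in advance.

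A non-significant comparison could be read as evidence of no difference because the protocol declared the cohorts adequately powered. A reader also cannot tell which definition of success the 85% refers to.

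**Working it through.** **Inputs from the article:** success 85% (event rate 15%); two-sided 95% interval; 5-point margin; 245–317 per cohort; 10% loss; 1,200 in four cohorts; 30 patients per surgeon (Study setting); the ECA rates in the table; a 5% reduction per component. **Assumptions:** 5% means percentage points; where composite rates are needed, they are built as shown.

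**1. The stated range.** Wald size: n = 1.96² × p(1−p)/0.05².
- At p = 0.85: 3.8415 × 0.1275/0.0025 = 195.9, so 196. Wilson gives 246 and exact (Clopper-Pearson) 254.
- At p = 0.80: Wald 246, exact 298.

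The lower end (245) is reproduced to within one patient. The upper end (317) is not reproduced by any two-sided method tried on the stated inputs. A near match needs an unstated input, such as 70% assurance: (1.96 + 0.524)² × 51 ≈ 315.

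**2. From requirement to total.**
- 300 × 0.9 = 270 evaluable per cohort.
- 317/0.9 = 352.2, so 353 per cohort and 353 × 4 = 1,412 (about 1,410).
- 245/0.9 = 272.2, so 273 per cohort and 1,092 in total.

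Neither end gives 1,200. Even 300 with no loss is below 317.

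**3. Precision at 270.** The Wald half-width is 1.96 × √(0.1275/270) = 4.3 points. The exact lower limit is 80.2%, which is 4.8 points below 85%. The target is met.

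**4. Power for one pair of cohorts.** With p̄ the mean of the two rates, power = Φ{[d − 1.96√(2p̄(1−p̄)/n)] / √([p₁(1−p₁) + p₂(1−p₂)]/n)}. For 15% vs 10%, n = 270: (0.05 − 1.96 × 0.02846)/0.02838 = −0.204, so 41.9%.

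Composites with 5 points off each component, if independent:
- Lowest ECA rates: 1 − 0.90 × 0.92 = 17.2% vs 1 − 0.95 × 0.97 = 7.9%.
- Highest ECA rates: 1 − 0.86 × 0.89 = 23.5% vs 1 − 0.91 × 0.94 = 14.5%.

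Under complete overlap the composite equals the larger component.

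| Reading of the 5-point difference | Rates | Power, 0.05 | Power, 0.05/6 |
|---|---|---|---|
| Wound infection alone | 10 vs 5; 14 vs 9 | 60%; 45% | 33%; 21% |
| Clavien IIIb-IV alone | 8 vs 3; 11 vs 6 | 72%; 55% | 46%; 29% |
| Composite, independent | 17.2 vs 7.9; 23.5 vs 14.5 | 91%; 76% | 74%; 51% |
| Composite, full overlap | 10 vs 5; 14 vs 9 | 60%; 45% | 33%; 21% |
| Composite, assumed | 15 vs 10 | 42% | 19% |

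If the 15% event rate is taken as the ICA rate instead, 20% vs 15% gives 33% (13% at 0.05/6).

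**5. Clustering.** With 30 × 0.9 = 27 evaluable per surgeon and an assumed ICC of 0.01–0.05, the design effect is 1 + 26 × ICC = 1.26–2.30. The effective n is 270/1.26 = 214 down to 270/2.30 = 117. The 42% falls to 35–21%. The independent-composite range of 76–91% falls to 66–83% at ICC 0.01 and 42–58% at ICC 0.05.

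**The case against.** The strongest defence is that the design is a precision design and the precision is delivered. 270 lies inside 245–317, 1,200 is stated as a minimum, and the 5-point target is met at 85%. This stands. A reader might infer that the cohorts are too small for their stated purpose, and the documents do not support that. What remains is an upper requirement that is neither met nor explained.

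A reader might also take 42% as the power for the stated effect. It is not. The 5 points are stated for each component, while the endpoint is either event, and the article gives no composite rate for ICA or ECA. Under independence one cohort pair has 76–91%, and if the components never coincide, 83–94%. The table's own gaps can also be larger than 5 points. Assuming independence, its smallest gap (17.2% vs 9.75%) gives 72% and its largest (23.5% vs 5.1%) nearly 100%. The stated effect is also for ICA vs ECA, not for one cohort pair. Pooled over approach (540 vs 540), the independent composite has 97–99% power and the full-overlap one 73–88%. So the power claim may be true for some contrasts. It is unsupported as a general statement.

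Two further inferences go too far. The article does not list six confirmatory pairwise tests: it calls simple comparisons exploratory and pairwise inference a posteriori, so missing familywise control is a weak point. Nor can it be said that the two-by-two structure is ignored, because regression models are planned and their terms may be left to the analysis plan.

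The planned re-sizing at interim is a real mitigation, but it does not supply the calculation behind a power claim made at the outset. Finally, the 10% loss has no time point. If 30-day loss is smaller, n is between 270 and 300, and 42% becomes at most 46%.

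**Conclusion.** The concern holds in this limited form. 1,200 recruited with 10% loss yields 270 per cohort, which is enough for the stated precision at 85% but 47 short of the upper requirement, and 317 does not follow from the stated inputs.

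The claim of sufficient power for multiple comparisons rests on no calculation and is not generally true. Across the tabulated readings of a 5-point reduction, power for one cohort pair runs from 42% to 91% unadjusted and from about 19% to 74% with Bonferroni for six pairs, before clustering. Only the independent composite exceeds 80%, and only for part of its range. Where the truth lies depends on the baseline rates, the overlap of the two components and the surgeon ICC. The article gives literature ranges for the first and nothing for the other two.

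The success bullets cannot be applied to a patient and contradict the composite in Outcomes. That conclusion needs no assumption.

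**What to change.** 1. State 270 evaluable per cohort after 10% loss, with the achieved precision (exact lower limit 80.2% at 85% success). Say which time point the 10% refers to.
2. Correct the 245–317 range or give the method and inputs that produce it. If 317 is to be kept as a requirement, the total becomes about 1,410.
3. Delete the power claim in both places, or replace it with the power range above and its assumptions on rates, overlap, alpha and clustering.
4. Remove the two group-level bullets as a definition of success and keep the patient-level composite in Outcomes. Present the 5 points only as a planning assumption for ICA vs ECA, and reconcile it with the statement that no differences are expected.

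Optionally, since Background sets out to compare both approach and anastomosis, estimate ICA vs ECA and robotic vs laparoscopic from all patients (540 vs 540), with the interaction reported. On the assumed 15% vs 10%, power rises from 42% to 70%.

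The cost of items 1, 3 and 4 is wording only. So is item 2, unless 317 is kept. The stated power will look less favourable. With the optional change, each main effect must be read beside the interaction.

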### Study setting

This will be an international, multicenter study that will take place over a 4-year period, including 2 years of follow-up. The centers chosen will be high volume (recommended > 30 minimally-invasive right colectomies per year) and participating centers should ideally have an implemented enhanced recovery after surgery protocol. All investigators will be qualified colorectal or general surgeons experienced in the surgical management of patients with colon lesions and who have a patient population fitting the study requirements. Surgeons must select one cohort which is understood that is their standard approach. Surgeons will have had completed ≥30 minimally-invasive right colectomy procedures for a colon tumor using their chosen technique, have published their experience or contributed videos for review by the principal investigator and submit pictures of the surgical field when a D3 Lymphadenectomy is performed during the study, and will contribute and consecutively maintain their technique on all eligible subjects during the enrolment phase. Surgeons meeting mentioned criteria will be selected by their technique in order to balance the inclusion of 300 patients in each arm. Different surgeons from the same institution may select different techniques. Surgeons will be able to include patients in any cohort of the study for which they are qualified, and will be asked to enrol at least 15 cases per chosen cohort, per year. It is estimated that each surgeon will include 30 patients in one of the cohorts of the study. This means that we estimate to include 40 surgeons from different centres in Geographical Europe. The number of participating centres will also be close to 40 as in most of the centres only one experienced surgeon will participate in the study. It is desirable that participating centers have an implemented Enhanced Recovery After Surgery (ERAS) protocol although perioperative management including ERAS protocol is difficult to standardize in all multicenter studies.

A screening log with all right colectomies excluded from the study will be kept at all institutions and uploaded to the eCRF.

### Interventions

Patients will be recruited to one of four cohorts, depending on the surgeon’s experience: 1) Robotic right colectomy with ICA; 2) robotic right colectomy with ECA; 3) laparoscopic right colectomy with ICA; 4) laparoscopic right colectomy with ECA. For the ICA cohorts, Pfannenstiel incision will be the chosen wound for specimen extraction. If an operation cannot be completed using any of these minimally-invasive techniques, the patient will be considered a conversion to open surgery. Per protocol, conversion is defined as when anything apart of the anastomosis has to be done through the laparotomy. If the anastomosis is not completely performed in an intracorporeal approach during an Intracorporeal Anastomosis Case, the case is considered also converted.

MIRCAST Study is an observational study which has all the advantages and limitations of an observational study. One of the main limitations is that the surgical technique will not be standardized. Different factors (wound protectors, antibiotics, bowel prep…) might have an impact in the co-primary endpoint. As standardizing the technique is not an option in an observational study, all factors that might have an influence in the co-primary endpoint will be registered in the electronic Case Report Forms.

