### Outcomes

The efficacy of the surgical method will be defined as the lack of surgical wound complications (infection, hematoma, hernia as late complication of wound infection…) and reduced severe complications. The primary composite endpoint will comprise two measures of success: Having either a surgical wound infection or a Clavien IIIb-IV postoperative complication constitute the primary composite endpoint. This means, that a patient having either a surgical wound infection or a Clavien IIIb-IV [10] complication would be scored as a “1”. Surgical wound infection will be assessed at the 30 postoperative day visit using specific wound assessment questions (purulent drainage, positive wound cultures, wound opened to drain and classical flogotic signs). These questions are recorded at the eCRF (Yes recorded as 1, No recorded as 0). In all cohorts, secondary endpoints will include oncologic results at 2 years, overall survival, disease-free survival, local recurrence, metastases rate, rate of unplanned conversions to open surgery, operative time (min), complete mesocolic excision, number of harvested lymph nodes, R0 resection, length of stay (days), ventral hernia (assessed 1 and 2 years after the right colectomy), patient-assessed quality of life measures (the European Organization for Research and Treatment of Cancer Quality of Life Questionnaires C30 and CR29), and systemic inflammatory response syndrome (C-reactive protein, with optional procalcitonin). Optional measures, to enable a medico-economic sub-study, include EQ-5D, time to ambulation, patient return to work/activity, pain evaluation, and resource utilization for procedure and follow-up care.

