Patients with missing data in planned surgical approach will be be excluded from the study. Patients with missing data in any end-point will be excluded from the analyses on that end-point, and patients with missing data in variables included in the propensity score will have their data imputed using multiple imputation procedures.

Three sensitivity analyses will be used for the primary end-points. The analysis will be repeated k times omitting a hospital each time (k = number of participant hospitals). In addition to intention-to-treat analysis, a sensitivity analysis will be conducted excluding patients with conversion. The analysis will be repeated stratifying by tertiles of the propensity score.

Stata/SE software will be used to perform the statistical analysis (versions 14–16 [forthcoming]).

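### Conversion has a second, ICA-only route, so the conversion endpoint is inflated in the intracorporeal cohorts and the exclusion sensitivity analysis treats ICA and ECA unequally

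*Protocol article*

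**What the plan says.** The Interventions section of the protocol article makes three statements about conversion.

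- General rule: "If an operation cannot be completed using any of these minimally-invasive techniques, the patient will be considered a conversion to open surgery". The four listed techniques include robotic and laparoscopic resection with extracorporeal anastomosis.
- Route A, all cohorts: "conversion is defined as when anything apart of the anastomosis has to be done through the laparotomy".
- Route B, ICA cohorts only: "If the anastomosis is not completely performed in an intracorporeal approach during an Intracorporeal Anastomosis Case, the case is considered also converted".

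Two planned analyses use the result. The Outcomes section lists, for all cohorts, the "rate of unplanned conversions to open surgery" as a secondary endpoint, and the Statistical analysis section says that "GLM with logit link will be used for unplanned conversion". For the primary endpoint, "a sensitivity analysis will be conducted excluding patients with conversion", alongside the intention-to-treat analysis. The main analysis does not depend on conversion status: "Patients from each cohort will be analyzed separately on an intent-to-treat basis".

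**The concern.** An ICA case can be converted by two routes and an ECA case by one. The event that triggers the second route, an anastomosis made outside the abdomen, is the planned procedure in the ECA cohorts. The same surgical event therefore scores as a conversion in one arm of the ICA-versus-ECA contrast and as routine in the other.

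For the secondary endpoint, part of any excess in the ICA cohorts would come from the definition and not from the surgery. Propensity adjustment or a hospital random effect cannot remove it, because it sits in the outcome and not in the case mix. For the sensitivity analysis, patients whose intracorporeal anastomosis failed leave the ICA cohorts, while ECA patients in whom it would have failed stay in. The comparison of anastomotic techniques is a main purpose of the study, so both matter for how its results are read.

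**Working it through.** The protocol gives no conversion rate and no power statement for conversion, so there is no figure to reproduce. The definitions are compared first. The sizes that follow are illustrations with assumed rates.

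**1. Definitions by cohort**

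| Event | ICA cohorts | ECA cohorts |
|---|---|---|
| Step other than anastomosis done through laparotomy (A) | converted | converted |
| Anastomosis completed extracorporeally (B) | converted | planned technique |

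Under the general rule, a case of type B has still been completed by one of the four listed techniques, so it is not a conversion to open surgery. Under the last sentence it is converted. The two sentences give different answers for the same patient.

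**2. Secondary endpoint**

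Inputs from the documents: 300 patients per cohort, or 600 against 600 if cohorts are pooled by anastomosis type (Patient recruitment); two-sided tests at 0.05 (Statistical analysis). Assumed: the same true route-A rate *c* in both groups, and a share *x* of ICA patients converted by route B alone.

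ECA rate = *c*; ICA rate = *c* + *x*; OR = [(c+x)/(1−c−x)] / [c/(1−c)].

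For *c* = 4%, *x* = 5%: ICA 9%, ECA 4%; OR = (0.09/0.91)/(0.04/0.96) = 0.0989/0.0417 = 2.37.

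The last two columns give the chance of p < 0.05 by the normal approximation for two proportions.

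| c | x | ICA vs ECA | OR | 300 vs 300 | 600 vs 600 |
|---|---|---|---|---|---|
| 6% | 1% | 7% vs 6% | 1.18 | 7% | 10% |
| 2% | 2% | 4% vs 2% | 2.04 | 30% | 53% |
| 4% | 3% | 7% vs 4% | 1.81 | 36% | 63% |
| 4% | 5% | 9% vs 4% | 2.37 | 70% | 94% |

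Over *c* = 2–6% and *x* = 1–8%, the odds ratio produced by the definition alone runs from 1.18 to 5.44.

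**3. Sensitivity analysis**

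Input from the documents: an 85% success rate, that is a 15% event rate (Patient recruitment). Assumed: the same 15% in both groups, and an event rate *r* among the share *x* of ICA patients removed by route B. Route-A conversions leave every cohort by the same rule and are left out of the sum.

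ICA event rate after exclusion = (0.15 − x·r)/(1 − x); ECA stays at 0.15.

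- *x* = 5%, *r* = 15%: (0.15 − 0.0075)/0.95 = 15.0%. No shift.
- *x* = 5%, *r* = 30%: (0.15 − 0.015)/0.95 = 14.2%. Shift −0.8 points, OR 0.94.
- *x* = 8%, *r* = 40%: (0.15 − 0.032)/0.92 = 12.8%. Shift −2.2 points, OR 0.83.

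The rule is unequal in every case. The estimate moves only when *r* differs from the rate in the other patients.

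**4. After the fix**

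With route A alone defining conversion, *x* drops out. The conversion odds ratio is 1.00 and the exclusion analysis gives 15.0% against 15.0% when the techniques do not differ.

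**The case against.** The endpoint is labelled as conversion to open surgery, and the general rule reserves that phrase for operations that none of the listed techniques could complete. The ICA clause says only that the case is converted. On that reading, ICA-to-ECA changes never enter the endpoint, and an analysis plan that is not shown may separate the two. This reading is possible, but the article does not state it. The clause follows directly on the definition of conversion and says the case is converted as well, which points towards pooling. The text needs correction on either reading.

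The broader definition also has a sensible use. A patient whose intracorporeal anastomosis was abandoned did not receive the planned technique, while an ECA patient anastomosed through the laparotomy did. Removing the former is reasonable in a per-protocol set. This stands, and it is a reason to keep such an analysis under its own label.

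A reader might go further and infer that the sensitivity analysis drops difficult patients from ICA only, or that it must favour ICA. The documents do not support either. Route-A conversions are excluded from all four cohorts; only the ICA-to-ECA group lacks a counterpart. A shift needs a different event risk in that group, and the documents give none. A higher risk is plausible and would favour ICA, but it is an assumption.

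**Conclusion.** The point holds for the definition and for the conversion endpoint. The ICA rate is raised relative to ECA whenever any ICA case is finished extracorporeally, and the sentences in Interventions contradict each other. The size is unknown. Under assumed rates it ranges from negligible (OR 1.18) to large enough to be declared significant more often than not (OR 2.37, 70% at 300 per group).

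For the sensitivity analysis the finding is limited to an unequal exclusion rule. The shift is zero at equal risk and about 2 points at the upper end of the assumptions tried.

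It would be wrong to infer that the main result is compromised. The primary intention-to-treat analysis does not use conversion status, and robotic-versus-laparoscopic contrasts within one anastomosis type share one definition. What is affected is one secondary endpoint and one of three sensitivity analyses, in ICA-versus-ECA contrasts only.

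**What to change.** 1. Reconcile the three sentences in Interventions.
2. For the secondary endpoint, use one definition of conversion to open surgery in all four cohorts: any step other than the anastomosis or specimen extraction done through the laparotomy.
3. Report change from intracorporeal to extracorporeal anastomosis as a separate technique-failure outcome in the ICA cohorts.
4. Run the exclusion sensitivity analysis on the common definition. If ICA-to-ECA cases are also to be excluded, show that as a separate analysis labelled per-protocol.
5. Keep intention-to-treat by planned technique as primary. Do not add an analysis by technique actually completed: it would move failed ICA cases into ECA and, if those cases carry higher risk, would flatter ICA and penalise ECA.

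The cost is a wording change and one extra derived variable, with no additional patients. The Data collection and management section says that the need for conversion is recorded, but does not say whether its type is. The sponsor must confirm that the eCRF distinguishes the two kinds.
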